### Challenges in current practice

While CTPA is widely available and has high diagnostic accuracy for detecting acute PE, growing demand places increasing pressure on radiology departments.^13^ These pressures, particularly during times of service strain, can contribute to delays in scan interpretation and increase the likelihood of fatigue-related diagnostic errors.^14^ Additionally, interobserver variability remains a persistent challenge. Non-specialist radiologists may differ in their ability to confidently identify prognostically significant features of radiological RHS despite their clinical relevance. Consequently, radiological reporting of the RV:LV ratio is often inconsistent or omitted altogether.^9 15^ This variability undermines the standardisation of acute PE care and may lead to missed opportunities for both escalation of treatment in high-risk patients and timely discharge in those identified as low risk.

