### Artificial intelligence in radiology

Artificial intelligence (AI) assisted image interpretation of CTPA scans offers a potential solution to these challenges. AI algorithms may enhance reporting accuracy, reduce inter-reporter variability, prioritise high-risk cases and support workflow efficiency for acute PE. AI tools have demonstrated strong performance compared with acute reporting radiologists in acute PE identification with reported sensitivities and specificities as high as 97% and 100% respectively.^16 17^ AI algorithms have also been shown to outperform radiologists in the detection of PE and improve reporting times through case prioritisation.^16 18^

Although AI algorithms for RHS are less well established, early studies suggest they can reliably quantify RV:LV ratio.^10^ Further validation of these algorithms in prospective populations and within the UK is required. Furthermore, few studies have evaluated the clinical utility or cost-effectiveness of integrating such AI software into radiology workflows in real-world settings.

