#### Exclusion criteria

Participants will not be eligible for inclusion in the study if any of the following are true:

Aged under 18 years old.Registered with the national opt-out scheme for research.CTPA performed for reasons other than the assessment of acute PE.CTPA reported by external radiologist.CTPA scan which is incomplete or discontinued.

Patients whose CTPA was reported by an external radiologist will be excluded due to difficulty confirming the reporting radiologist’s access to existing AI software. Patients will also be excluded if the clinical indication for CTPA is unrelated to acute PE. The AI software is solely licenced for the assessment of acute PE. No substantial amendments have been made to the eligibility criteria since study inception.

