### Sample size

As a pragmatic real-world quasi-experimental assessment of AI integration, formal power calculations were not feasible. Based on historic imaging volumes, it is anticipated that approximately 3500 eligible CTPAs will be identified across the 24-month recruitment period and that the prevalence of acute PE will be between 12% and 15%.

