Exploratory outcomes	Given the exploratory nature of this observational non-randomised feasibility study, there may be patterns/outcomes which emerge/develop during the study period. The investigators will report on any patterns that may emerge following the introduction of AI reporting

AI, artificial intelligence; CTPA, CT pulmonary angiography; PE, pulmonary embolism; RV:LV, right ventricular to left ventricular ratio.

Descriptive statistics will summarise participant baseline characteristics and comorbidities, separately in the comparator and intervention cohorts. Our primary analyses will consist of comparisons between the comparator and intervention cohorts, with continuous outcomes analysed using t-tests and categorical outcomes using χ^2^ tests. To account for and disentangle any possible underlying time trends from the effects of AI introduction, regression models will be used to compare outcomes. These will include covariates that allow for a linear trend in the pre-implementation phase, a step change at the point of AI implementation, and a modification to the linear trend following this.

Kaplan-Meier survival curves will quantify differences between time-to-event outcomes in the two cohorts. Cox regression models will also be used to summarise the difference between cohorts. If feasible, regression models will be adjusted for known predictors of outcome from both Geneva and sPESI scoring systems.^20 21^ Missing values will be handled by performing each analysis excluding patients who have relevant data missing for the variables concerned. Statistical significance will be set according to p value <0.05.

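### The planned before/after analyses have no term for the reporting radiologist, so if the mix of in-house readers changes between the two years, that change would be counted as an AI effect

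*Protocol article*

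**What the plan says.** The statistical analysis section (Clinical and radiological outcomes) makes unadjusted comparisons of the two cohorts the primary analyses, "with continuous outcomes analysed using t-tests and categorical outcomes using" chi-squared tests. "Statistical significance will be set according to p value <0.05". Regression models then add a linear trend before implementation, a step at implementation and a change in trend afterwards. If feasible, they also adjust for predictors from the Geneva and sPESI scores. All of these are calendar or patient-level terms. The list under Participant data does not include the identity or grade of the reporting radiologist.

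Other sections give the reader a central part:

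- Challenges in current practice: "Non-specialist radiologists may differ in their ability to confidently identify prognostically significant features of radiological RHS", and interobserver variability is described as a continuing problem.
- Intervention cohort: each reporting radiologist decides whether to take the AI output into account.
- Clinical management: differences in outcome are expected to reflect what radiologists do with the AI findings and how clinicians then act.
- Study design: exposure is set by calendar period, not by randomisation.
- Exclusion criteria: one exclusion is "CTPA reported by external radiologist". This restricts the pool to in-house readers but does not hold their mix constant.

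**The concern.** In a before/after design, anything that changes at the same time as exposure is confounded with it. The article recognises this for underlying time trends and models them. Who reads the scans is another such factor, and it lies directly on the path through which the AI is meant to act.

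If readers differ in how often they comment on RHS, and if their shares of the workload or their membership differ between the two years, then RHS reporting, PE risk class and, less directly, the proportion of guideline-concordant decisions can move without the AI contributing anything.

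The segmented terms do not remove this. A reader change at go-live falls into the step, and one after go-live falls into the change in trend. Those two terms are the AI effect estimate. Only a gradual drift already under way before go-live would be absorbed.

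**Working it through.** **No planned figure to reproduce.** The Sample size section says "formal power calculations were not feasible". The only stated error rate is 0.05 (taken as two-sided).

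**Inputs from the article.** "approximately 3500 eligible CTPAs will be identified across the 24-month recruitment period", with PE prevalence of 12% to 15%. With an even split, 3500 / 2 = 1750 scans per cohort, so 0.12 × 1750 = 210 to 0.15 × 1750 = 262 PE cases per cohort.

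**Assumptions not in the article.** Outcome rate 60%; number of readers K; between-reader variation, as an ICC or a logit SD; share of readers replaced, r; unequal workloads w (Dirichlet, parameter 3, so the expected sum of w² is 4 / (3K + 1)).

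**Formula.** With no AI effect, the variance of the between-cohort difference, relative to what the chi-squared test assumes, is about

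V = 1 + ICC × n × r × Σw²

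and the rejection rate is 2 × [1 − Φ(1.96 / √V)]. With r = 0 and unchanged shares, V = 1 and the rate is 5%.

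**Check against simulation.**

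- n = 210, K = 12 (Σw² = 4/37 = 0.108), ICC 0.05, r = 0.25: V = 1 + 0.05 × 210 × 0.25 × 0.108 = 1.28, rejection 0.084. Simulated: 0.082.
- n = 262, K = 12, ICC 0.10, r = 0.50: V = 1 + 0.10 × 262 × 0.50 × 0.108 = 2.42, rejection 0.207. Simulated: 0.206.

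**Corners of the range quoted (logit SD 0.4 to 0.8, K = 8 to 20, r = 15% to 25%).**

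- Mild: SD 0.4 gives ICC of about 0.6 × 0.4 × 0.4² = 0.038. With K = 20 (Σw² = 4/61 = 0.066), r = 0.15, n = 210: V = 1.08, rejection 0.059.
- Strong: SD 0.8 gives ICC of about 0.12 (by numerical integration; the first-order formula gives 0.15, which is too high here). With K = 8 (Σw² = 4/25 = 0.16), r = 0.25, n = 262: V = 1 + 0.12 × 262 × 0.25 × 0.16 = 2.26, rejection 0.19.

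This matches the simulated range of about 6% to 19%.

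**Simulated rejection rates with no AI effect, by ICC (12 or 25 readers, 210 or 262 cases per cohort).**

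| Reader mix | ICC 0.01 | ICC 0.05 | ICC 0.10 |
|---|---|---|---|
| Unchanged | 0.049–0.054 | 0.048–0.051 | 0.050–0.053 |
| Same readers, shifted workloads | 0.050–0.056 | 0.067–0.079 | 0.086–0.098 |
| 25% replaced | 0.056–0.061 | 0.061–0.084 | 0.081–0.129 |
| 50% replaced | 0.056–0.064 | 0.084–0.136 | 0.121–0.206 |

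**The same point as a bias.** Bias = share of scans moved × difference between reader groups. With n = 210 the standard error is √(2 × 0.24 / 210) = 0.048.

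- Moving 20% of scans between groups 10 points apart: 0.20 × 0.10 = 2 points, rejection 0.07.
- Moving 30% between groups 20 points apart: 0.30 × 0.20 = 6 points, rejection 0.24 (0.29 with n = 262).

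**With the reader in the analysis.** A Mantel-Haenszel test stratified by reader rejects in 4.4% to 5.6% of runs across the table's scenarios. It keeps only about 75% of patients with 25% of readers replaced, and about 50% with half replaced. A radiologist random intercept, under 8 to 20 readers and SD 0.4 to 0.8, rejects in about 4% to 7%, with a standard error at most about 7% larger.

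**The case against.** The strongest reply is that the condition may never arise. Nothing in the article says that staffing or workload shares changed, and the number of readers, their spread and their turnover are all assumed. The upper end needs a wide spread: SD 0.8 around 60% puts 95% of readers between about 24% and 88%, which is a lot for a decision that also depends on the treating clinicians. At ICC 0.01 with a quarter of readers replaced, the rate is only about 6%. This stands. It limits the size, and it is why the point is conditional.

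A reader might infer three stronger things that the article does not support:

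- That treating one radiologist's reports as independent inflates the error rate by itself. It does not: with an unchanged mix the rate is about 5% at every ICC tried.
- That the article says readers do differ on all outcomes. It says they may, and only about RHS features.
- That the study leaves one of its own outcomes unexamined because AI may "reduce inter-reporter variability". That phrase is background on AI in general, not a listed objective or outcome.

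It can also be said that random-effect structure belongs in a separate analysis plan. That would answer mere silence. Here, however, the article itself fixes unadjusted tests as primary and names calendar and patient-level covariates only. The external-reporter exclusion shows that internal or external status must be known. It does not prove that an individual reader code is being extracted.

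**Conclusion.** The point holds as a conditional weakness of the stated analysis. If in-house readers differ and their mix changes at or after go-live, the planned tests and the step and trend-change terms attribute that change to the AI.

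For PE-only outcomes the false-positive rate is about 6% to 19% under 8 to 20 readers, logit SD 0.4 to 0.8 and 15% to 25% turnover, and near 5% with a stable mix. Those inputs are assumptions. The risk is greatest for RHS reporting and risk class, and smaller for the primary outcome, which also passes through clinicians. Outcomes that concern the AI output itself, such as its failure rate, are not affected. A change is worthwhile because it is cheap and because a stable reader mix, if shown, would support the attribution made under Clinical management.

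**What to change.** 1. Take a pseudonymised reporting-radiologist code from the radiology information system, which is already used to screen the cohorts, and add it to the case report form for both years. Its availability should be confirmed.
2. Tabulate the share of scans, and of PE cases, by reader and cohort.
3. Add a radiologist random intercept to the before/after models for report-dependent outcomes (RHS reporting, risk class, guideline-concordant decisions), and base the AI conclusion on that estimate. The unadjusted tests can be kept as descriptive.
4. Add a sensitivity analysis limited to radiologists who reported in both periods.

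A random AI effect by reader and the between-reader spread before and after are optional and exploratory. With 20 readers there are only about 210 / 20 = 10 to 262 / 20 = 13 PE cases per reader per year, so a reader-specific AI effect would be poorly estimated.

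The cost is one extra data field, intervals a few percent wider when readers change (standard error at most about 7% larger in the settings simulated), and fewer patients in the sensitivity analysis, about 75% of them if a quarter of readers are replaced.

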### Study population and setting

Study participants will be recruited from consecutive, clinically indicated CTPAs performed for the assessment of acute PE at Royal United Hospitals Bath NHS Foundation Trust in England. Scans from both inpatient and outpatient settings will be included. Ethical approval for participant inclusion has been granted by West of Scotland Research Ethics Service (23/WS/0067, 3 May 2023).

The pre-implementation (comparator) cohort will be retrospectively identified over a 12-month period preceding AI deployment. Following a 1 month implementation phase, the post-implementation (intervention) cohort will be prospectively recruited over the subsequent 12 months. Prospective recruitment will complete on 7th January 2025.

All participants will meet the following eligibility criteria:

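### With one year either side and no seasonal term named, the segmented regression can bias the AI step by 0 to about 2 times any yearly amplitude, depending on when the cycle peaks

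*Protocol article*

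**What the plan says.** The Protocol article, under Clinical and radiological outcomes, gives the regression a specific task: "To account for and disentangle any possible underlying time trends from the effects of AI introduction, regression models will be used to compare outcomes". It then lists the time terms: "These will include covariates that allow for a linear trend in the pre-implementation phase, a step change at the point of AI implementation". A third term lets the slope differ once AI is in use. The only other adjustment mentioned is clinical: "If feasible, regression models will be adjusted for known predictors of outcome from both Geneva and sPESI scoring systems". No harmonic, calendar-month or other seasonal term is named.

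The same section makes the unadjusted cohort comparison primary: "Our primary analyses will consist of comparisons between the comparator and intervention cohorts", by t-test or chi-square test.

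The windows are in Study population and setting: "The pre-implementation (comparator) cohort will be retrospectively identified over a 12-month period preceding AI deployment"; then, after a 1-month implementation phase, "the post-implementation (intervention) cohort will be prospectively recruited over the subsequent 12 months". Recruitment ends on 7 January 2025. The implied dates are therefore about 8 December 2022 to 7 December 2023 (before), 8 December 2023 to 7 January 2024 (gap) and 8 January 2024 to 7 January 2025 (after).

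**The concern.** A straight line fitted to exactly one yearly cycle usually tilts, because the cycle is rarely symmetric about the middle of the window. Two tilted lines that meet at the implementation gap leave a mismatch there, and the model reports it as a step or a change of slope. The interval does not reflect this bias.

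In a non-randomised before/after study, readers will tend to trust the trend-adjusted estimate more than the crude one, because it is there to deal with time. If the two disagree because of season, the biased one may be preferred.

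Seasonality is plausible for the operational outcomes in Table 1 (bed days, time to anticoagulation, time to discharge). The background section links delays and errors in scan interpretation to workload, "particularly during times of service strain". It does not say that the strain is yearly or falls in winter.

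**Working it through.** The protocol states no step estimate or power figure, so there is nothing to reproduce.

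**Inputs from the documents.** 12 months before, 1-month gap, 12 months after; end date 7 January 2025; about 3500 scans; PE prevalence 12% to 15%; significance level 0.05.

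**Assumptions.** Equal split between cohorts, giving 3500 × 0.12 / 2 = 210 to 3500 × 0.15 / 2 = 262 PE cases each; even recruitment within each window; two-sided test; outcome assessed in PE cases; the same yearly cosine of amplitude A in both years (peak to trough 2A); true step and true trend both zero.

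**Bias per unit of amplitude.** Let time run from 0 to 12 and 13 to 25 months, with the peak at p.
- The least-squares slope over one full cycle centred at m is -(A/2π) sin[30°(m - p)] per month, and the window mean is zero.
- The window centres are 6 and 19. The step is read at mid-gap (12.5, about 23 December), which is 6.5 months from each centre.
- Let d be the number of months from mid-gap to the peak.
- Step = (6.5/π) × 0.9659 × A sin(30°d) = 2.00A sin(30°d).
- Slope change = (12/π) × 0.2588 × A cos(30°d) = 0.99A cos(30°d) per year.
- Simple before/after difference = 0 - 0 = 0.

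| Peak | d | False step | False slope change per year |
|---|---|---|---|
| about 23 Dec | 0 | 0 | +0.99A |
| mid-Dec | -0.25 | -0.26A | +0.98A |
| mid-Jan | 0.75 | +0.76A | +0.91A |
| mid-Feb | 1.75 | +1.59A | +0.60A |
| about 23 Mar | 3 | +2.00A | 0 |
| about 23 Sep | 9 | -2.00A | 0 |

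Reading the step at either edge of the gap moves these values by about 0.04A at most. In round terms they are -0.3A, 0.8A, 1.6A and 2.0A.

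**Precision.** The step variance is 4.54 times that of the simple contrast, so its SE is √4.54 = 2.13 times as large. With a sine-cosine pair added the ratio is 9.16 (3.03 times). The increase is √(9.16/4.54) = 1.42. With the largest binomial variance, the step SE is 2.13 × √(0.5/n) = 10.4 points (n = 210) or 9.3 points (n = 262).

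**Type I error for a true zero step.** With δ = bias/SE, the rate is Φ(-1.96 + δ) + Φ(-1.96 - δ).

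| Step bias | A = 5: points | Type I error | A = 10: points | Type I error |
|---|---|---|---|---|
| 0 | 0 | 5% | 0 | 5% |
| 0.3A (mid-Dec) | 1.5 | 5% | 3 | 6% |
| 0.8A (mid-Jan) | 4 | 7% | 8 | 12-14% |
| 1.6A (mid-Feb) | 8 | 12-14% | 16 | 34-40% |
| 2.0A (late Mar/Sep) | 10 | 16-19% | 20 | 49-57% |

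A simulation with a 60% baseline and robust standard errors agrees. At A = 5 the step test rejected in 6% to 8% of runs (January peak), 12% to 15% (February) and 14% to 20% (April or October). The chi-square test stayed at about 5%. With the sine-cosine pair, the mean false step was about 0 and rejection was between about 4% and 7.5%.

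**The case against.** **The article is condensed.** Its list of covariates is not exclusive, and the analysis plan is not shown. That stands to this extent: if the full plan already has a seasonal term, the point is met. But the article states both the time terms and the window lengths, and following those terms as written can give a biased step. That is more than missing detail.

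**The primary analyses are unaffected.** This stands. Both windows cover a full year, so a stable yearly cycle cancels. A reader might infer that the primary result is biased; it is not. A large step beside a null primary contrast would also be visible.

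**The false step is not automatic.** This stands too. A reader might infer that any yearly cycle must produce one, or that winter pressure alone could give the worst case. The step bias vanishes for a peak or trough near 23 December, inside the implied gap. December to February peaks give at most about 1.6A, and the 2A figure needs a spring or autumn peak. Where the step is safe, however, the slope change is not.

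**The amplitude has no source in the documents.** Correct. A 5-point amplitude means a 10-point swing from peak to trough, and no section says that any outcome is seasonal.

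**Harmonics everywhere could cost more than they save.** At A = 5 and a mid-January peak, the root mean squared error of the step is 10.1 to 11.1 points without the pair and 13.2 to 14.8 with it. At the worst phase it is 13.7 to 14.4 against 13.2 to 14.8. This argues against replacing the stated model, but not against a sensitivity analysis.

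**Conclusion.** The point holds in a limited form. With the stated terms and windows, a stable yearly cycle can bias the step by 0 to about 2.0A, and the slope change by up to about 1A per year where the step bias is small. These multiples follow from the design and need no assumption about A, but they do assume even recruitment and the same sinusoid in both years. The sizes in percentage points rest on an assumed amplitude. At 5 points the false step is 0 to 10 points, or 0 to 8 for December to February peaks, with type I error of about 5% to 19%. The weakness lies in the secondary, trend-adjusted estimate and not in the primary comparisons.

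**What to change.** Keep the segmented model as stated. Prespecify a sensitivity analysis that adds one sine-cosine pair with a 12-month period, shared by both years; it can be estimated because two full cycles are observed. Report the before/after contrast beside both. State in advance that a step or slope change will not be read as an AI effect unless it persists in the sensitivity model and is consistent with that contrast.

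The cost is a sentence or two in the analysis plan and two degrees of freedom. In the sensitivity model the step's standard error is about 42% larger: under the inputs above it rises from 9.3-10.4 to 13.2-14.8 points. The pair also assumes the same cycle in both years, which two years of data can hardly test.

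If the full analysis plan already contains such a term, it is enough to say so.

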### Study objectives

The retrospective cohort analysis will assess the diagnostic performance of AI in detecting acute PE and quantifying associated RHS. The study will compare AI outputs against routine clinical radiology reports as well as a redefined ground truth through expert thoracic radiologist review of a subset of retrospective CTPAs. The prospective cohort analysis will assess the real-world impact of AI integration on clinical practice, including risk stratification, treatment decisions and patient outcomes. The study will compare concordance of acute PE risk stratification and patient management with local protocols and European Society of Cardiology guidelines.^11^ The study will also assess the clinical-cost impact of AI integration into radiology workflows.

Finally, the study will explore the perspective of key stakeholders, including radiologists and referring clinicians, on the implementation and use of AI technology before, during and after deployment.

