### Interventions

#### CT report interpretation

All radiology reports for consecutive CTPAs in the comparator and intervention cohorts will be reviewed by a respiratory registrar with 8 years’ clinical experience. The reports will be classified as either positive or negative for acute PE. In cases of uncertainty, adjudication will be performed by a second senior clinician.

The same registrar and a second clinician, blinded to each other’s decisions, will independently assess the reports for radiologist assessment of RHS. Reports will be categorised as either positive, negative or ‘no comment’ for RHS. Discrepancies will be resolved through discussion and, if required, arbitration from a third clinician. This approach will establish a consistent comparator for evaluating AI outputs.

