##### Clinical management

Royal United Hospitals Bath NHS Foundation Trust does not currently have a dedicated Pulmonary Embolism Response Team or onsite percutaneous thrombectomy service. There are no plans to implement either of these during the study period. Consequently, acute PE management follows standard clinical pathways.

The AI acts as an adjunct to routine clinical care, supporting detection of acute PE and automated assessment of RHS. We therefore anticipate any outcome differences will reflect how radiologists incorporate AI-derived findings into their reports and how clinicians act on them, rather than the influence of specialist services or advanced interventional pathways.

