### Statistical analysis

#### Clinical and radiological outcomes

Our primary outcome will be the proportion of patient decisions made in line with evidence-based best practice guidelines after introducing AI technology within CTPA reporting. Secondary outcomes relate to acute PE detection, RV:LV ratio quantification and clinical and operational endpoints including mortality, length of stay, readmission, follow-up and cost to NHS (table 1).

**Table 1 T1:** Primary, secondary and additional outcomes

Outcome measure	Measure description
Primary outcome measure	
Proportion of patient decisions made in line with evidence-based best practice guidelines after introducing AI technology within CTPA reporting	Comparison before and after AI introduction
Secondary outcome measures	
Rate of acute PE detection with AI technology	True positives and true negatives
Rate of discordant acute PE cases	False positive and false negative rate with acute PE detection
AI failure rate for acute PE detection	Proportion of scans unable to be interpreted by AI despite suitable CTPA acquisition
Rate of RV:LV detection with AI technology	True positive and true negative
Rate of discordant RV:LV detection	False positive and false negative
Failure rate for automated RV:LV ratio	Proportion of scans unable to calculate automated RV:LV ratio despite suitable CTPA acquisition
30-day mortality	Patient mortality (death) at 30-days post-PE diagnosis. Comparison before and after AI introduction
12-month mortality	Patient mortality (death) at 12 months post-PE diagnosis. Comparison before and after AI introduction
Hospital admission and bed days for acute PE	Comparison before and after AI introduction
Time to anticoagulation in PE cases	Comparison before and after AI introduction
Time from CTPA to discharge	Comparison before and after AI introduction
PE risk stratification rates (low, intermediate low, intermediate high and high risk)	Comparison before and after AI introduction
Cost to NHS for acute PE	Comparison before and after AI introduction
End-user (clinician and radiologist) acceptability of AI technology	Quantified metrics from a non-validated questionnaire to evaluate end-use experience of integrated AI radiology reporting
Referral rates to outpatient follow-up (respiratory, thrombosis, haematology)	Comparison before and after AI introduction
Diagnostic rate of chronic thromboembolic pulmonary hypertension	Comparison before and after AI introduction
Additional outcome measures	

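### Complete-case exclusion in every analysis can remove patients whose right heart strain was not reported, and so distort the before/after contrast in the primary outcome and the risk classes

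*Protocol article*

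**What the plan says.** All references are to the protocol article.

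- **Missing data** (Clinical and radiological outcomes): "Missing values will be handled by performing each analysis excluding patients who have relevant data missing for the variables concerned". No outcome is exempted and no sensitivity analysis is named.
- **Primary outcome** (same section): "Our primary outcome will be the proportion of patient decisions made in line with evidence-based best practice guidelines after introducing AI technology within CTPA reporting". The yardstick is under Study objectives: "The study will compare concordance of acute PE risk stratification and patient management with local protocols and European Society of Cardiology guidelines". Concordance therefore covers risk stratification as well as management.
- **Risk classes** (Table 1): four classes, from low to high, are compared before and after AI. There is no class for a patient who cannot be classified.
- **Usual care** (Challenges in current practice): "radiological reporting of the RV:LV ratio is often inconsistent or omitted altogether". The section goes on to say that this variability may cost high-risk patients escalation and low-risk patients timely discharge.
- **Coding of reports** (CT report interpretation): "Reports will be categorised as either positive, negative or" a third code, 'no comment'.
- **Role of the AI** (Clinical management): "The AI acts as an adjunct to routine clinical care, supporting detection of acute PE and automated assessment of RHS". In the comparator cohort it is run only in retrospect and cannot affect care.
- **AI failures** (Table 1): a separate secondary outcome, "Proportion of scans unable to be interpreted by AI despite suitable CTPA acquisition", with a parallel failure rate for the RV:LV ratio.

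**The concern.** Excluding incomplete cases is harmless only under conditions that this study's own rationale argues against. Whether RHS is commented on is determined after the intervention and lies on the pathway by which the AI is meant to work: a better report, then better risk stratification, then a better decision. The protocol gives reason to expect more unreported RHS before AI than after, and worse decisions where it is unreported. Restricting the analysis to assessed patients conditions on that pathway, and would take more of the poorly served patients out of the comparator cohort than out of the intervention cohort.

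The protocol does not say how a 'no comment' report or an unmeasured biomarker counts in the primary outcome or in the four risk classes. For a patient who cannot be classified, the only stated instruction is to exclude. At stake are the primary comparison and the risk-stratification outcome. The same rule would also drop patients with any missing Geneva or sPESI item from the adjusted regression models.

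**Working it through.** The protocol states no power, effect size or missingness rate, so there is no figure to reproduce.

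**Inputs from the protocol** (Sample size): about 3500 scans over 24 months and PE prevalence of 12% to 15%. PE cases = 3500 × 0.12 = 420 to 3500 × 0.15 = 525. With equal cohorts (assumed) that is 210 to 262 per cohort.

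**Assumed inputs.** m0 and m1 are the shares not assessed before and after AI. c_a and c_u are concordance if assessed and if not assessed, first taken as the same in both cohorts. The denominator is taken as PE patients.

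**Formulas.**
- All patients: concordance = (1 − m)·c_a + m·c_u, so the difference is (m0 − m1)·(c_a − c_u).
- Complete cases: concordance = c_a in both cohorts, so the difference is 0 whatever the true one is.

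| m0 / m1 | c_a / c_u | All patients | Difference | Complete cases |
|---|---|---|---|---|
| 40% / 10% | 70% / 40% | 58% vs 67% | +9 points | 70% vs 70% |
| 50% / 10% | 80% / 40% | 60% vs 76% | +16 points | 80% vs 80% |
| 40% / 10% | 80% / 40% | 64% vs 76% | +12 points | 80% vs 80% |
| 20% / 5% | 80% / 40% | 72% vs 78% | +6 points | 80% vs 80% |

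First row in full: 0.6 × 0.70 + 0.4 × 0.40 = 0.58 and 0.9 × 0.70 + 0.1 × 0.40 = 0.67.

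With 210 to 262 per cohort and a two-sided 5% test (sidedness assumed), power for the all-patient contrast is 94% to 98% for 16 points, 77% to 85% for 12 and 29% to 35% for 6. In the second row, complete-case exclusion leaves 105 to 131 patients before AI against 189 to 236 after.

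**Reversal.** Let patients newly assessed because of the AI have 60% concordance, with 80% in those who would be assessed anyway, 40% in the unassessed, and m = 50% and 10%.
- All patients: before, 0.5 × 0.80 + 0.5 × 0.40 = 0.60. After, 0.5 × 0.80 + 0.4 × 0.60 + 0.1 × 0.40 = 0.68. Difference +8 points.
- Complete cases: before, 0.80. After, (0.40 + 0.24) / 0.90 = 0.711. Difference about −9 points.

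**When the problem disappears.** In the first model the two analyses agree if m0 = m1 (30% and 30%: 0 and 0) or if c_a = c_u (80% and 80%: 0 and 0).

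**AI accuracy.** If a share f of scans fails regardless of PE status and failures in PE-positive scans count as misses, sensitivity becomes (1 − f) × sensitivity. For an assumed 93%, f = 2%, 5% and 10% give 91%, 88% and 84%. Counting failures in PE-negative scans as true negatives would raise specificity, since (1 − f) × specificity + f exceeds specificity. At 12% to 15% prevalence, 85% to 88% of scans are PE-negative.

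**The case against.** The strongest reply is that the rule excludes only patients with relevant data missing. 'No comment' is one of three defined codes, hence an observed value, and a decision taken without an RHS comment was still taken and can still be judged. This stands. A reader might infer that the protocol drops every patient whose RHS went unreported, but no section says so. Exclusion follows only if that code is treated as missing or the patient as unclassifiable.

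Other objections also stand in part.

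- **Troponin.** A reader might count absent troponin among the deficits that the AI corrects. The AI detects PE and assesses RHS; it does not supply troponin, and nothing says that missing values cluster in the comparator cohort. Absence matters only where it leaves a patient unclassifiable.
- **Imbalance.** Radiologists may use or ignore the AI output and no report is filled in automatically, so fewer unreported cases after AI is an expectation, not a fact.
- **Magnitude.** Setting concordance among assessed patients equal in both cohorts forces the complete-case difference to 0. The table shows what can happen, not what will.
- **AI failures.** Their rates are already planned outcomes, the missing-data sentence sits outside the AI accuracy section, and unanalysed scans are still read by a radiologist. It cannot be said that the plan hides failures.
- **Scoring every unassessed patient as not in line.** This could build the AI's direct output into the primary outcome with no change in any decision, so it should not be the primary rule.

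It can also be said that derivation rules and sensitivity analyses belong in an analysis plan that is not shown. Their absence from an article is indeed no finding. The finding is the rule that the article does state, for each analysis and without qualification.

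**Conclusion.** The concern holds in conditional form. The stated rule, applied to patients with RHS 'no comment' or an unmeasured biomarker, can shrink, erase or reverse the before/after contrast in the primary outcome and in the four risk classes. Two premises carry this: non-assessment is more common before AI than after, and it relates to decision quality. The protocol's text supports the direction of both and quantifies neither. The size is therefore unknown. The change from +9 points to 0, and the reversal from +8 to about −9, rest wholly on assumed rates, and there is no distortion in the simple model if either premise fails. The documents do not support saying that the primary result will be biased, or by how much. The AI accuracy point is secondary and concerns how results are presented.

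**What to change.** Replace the single rule, before analysis, with the following.

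1. State that 'no comment' and an unmeasured biomarker are observed process information, not missing data.
2. Keep every PE patient in the primary denominator and judge the decision actually made against the local protocols and European guideline named under Study objectives. Add two bounding sensitivity analyses that score unassessable decisions all as in line and all as not in line.
3. Add a 'not risk-stratified' category to the risk-stratification outcome.
4. Use multiple imputation for missing Geneva and sPESI covariates in the adjusted regression models.
5. Keep complete case as a sensitivity analysis.
6. For AI accuracy, report results excluding failed scans and again with failures counted against the AI: as misses in PE-positive scans, and not as true negatives in PE-negative scans. Show both beside the planned failure rates.

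The cost is revised wording and a little more analysis. No new data are needed.
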